## **6. TREATMENT OF SUBJECT**

After getting informed consent and ascertainment of eligibility, consenting eligible subjects will be entered into the trial in the randomization sequence, as noted earlier.

During administration of the agents, necessary numbers of vials with consecutive serial numbers (starting with Serial No. 1) will be at hand. The agent to be administered will be determined by the subject serial number which shall be the same as the serial number on the vial. The subject will drink a buffer solution (bicarbonates 2.5g and ascorbic acid 1.65g in 100 ml). The freeze dried vaccine or placebo vials will be reconstituted in 1ml of diluents provided by the manufacturer and given directly into mouth to drink 5 minutes after drinking the buffer solution. This will be followed by water ad-libitum. The agent will be administered with a disposable syringe (without needle). At the time of the vaccine dose, information about vaccine administration will be entered in the CRF 1. This information will note the code (serial number) of the assigned agent; the success of administration as well as certain additional information. If it is judged that a dose is not successfully ingested (e.g. regurgitated, spat out) recipients will be offered a replacement dose as per the discretion of PI.

The subject will not receive any other medicine unless indicated and a Medication Form will be filled. Study Doctor will decide about the medication; however antibiotics will be avoided if practical until they receive a single dose of Doxycycline or Azithromycin on day 21.

## 7. ASSESSMENT OF EFFICACY

**7. 1.** For serum vibriocidal responses (defined as  $\geq 4$  fold increase either at day 7 or 8) in  $\geq 30\%$  of the vaccine recipients will be considered as the vaccine having acceptable level of efficacy. The paired sera will be tested after completion of recruitment and follow-up.

**7.2.** For diarrheal adverse events, a rate lower than 10% incremental rate over the placebo group will be considered acceptable level of response. Analysis of adverse diarrheal events will be analyzed after completion of the study.

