#### **4.11. Sample Size**

A 1 –sided 95%confidence interval was used to calculate the sample size since this allowed us to rule out clinically unacceptable high rates of diarrheal adverse event occurring during the 3 days after either dose as well as establish that the vaccine induced adequate seroconversion to V. cholerae O1 Inaba among recipients [11].

Assuming a 10% diarrheal rate among placebo and vaccine recipients alike, to exclude a vaccine-placebo difference in the rate of diarrhea of greater than 20% (upper boundary of the 1-tailed 95% confidence interval) with a power of 0.9, the minimum number of subjects required for each group is 39. For serum vibriocidal responses, assuming a background rate of 5% seroconversion among placebo recipients after one dose and a true vibriocidal response in the vaccine group of 60%, to exclude a vaccine-placebo difference of 30% (lower boundary of the 1-tailed 95% confidence interval) with a power of 0.9, the minimum of subjects required for each group was 40. To adjust for the number of persons expected to drop out of the study, at least 44 persons are therefore required in each group.

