#### **4.12. Interpretation of the results:**

- (a) Acceptable level of adverse events mainly diarrhea, vomiting (see 4.11) is a necessary condition for field trial.
- (b) Similar rise in vibriocidal antibody titre (8) as after VA 1.3 is necessary for going into a field trial (same or above the lower 95% CI confidence interval i.e. 49%).

Vibriocidal antibody is not regarded as a protective antibody against cholera, rather a surrogate marker of protection. It has been surmised from field studies in cholera endemic population where higher vibriocidal antibody titre (presumably from inapparent infection or mild disease due to cholera) is associated with less likelihood of clinical cholera. Based on these observations vibriocidal antibody titre has been used as a crude proxy for protection after administration of a candidate vaccine. However comparing a killed oral vaccine with a live oral vaccine using this proxy indicator for protection is likely to be misleading. One important difference is the ability of the live vaccine to colonize the intestine albeit for a brief period with relevant biological and immunological responses that may not be reflected in vibriocidal antibody rise.

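### Section 7.1 accepts a 30% response among vaccinees alone, which conflicts with the difference-based criterion in 4.11 and lies far below the 49% field-trial condition in 4.12(b)

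*Protocol*

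**What the plan says.** Three places in the protocol set a bar for the vibriocidal response.

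- **Section 7.1 (Assessment of efficacy).** A rise of at least fourfold at day 7 or 8 in at least 30% "of the vaccine recipients will be considered as the vaccine having acceptable level of efficacy". The threshold has no placebo term and no confidence limit.
- **Section 4.11 (Sample size).** The stated purpose includes establishing adequate seroconversion. The planning values are "assuming a background rate of 5% seroconversion among placebo recipients after one dose" and "a true vibriocidal response in the vaccine group of 60"%. The target is "to exclude a vaccine-placebo difference of 30% (lower boundary of the 1-tailed 95% confidence interval) with a power of 0.9", which gives 40 per group, raised to 44 for dropout.
- **Section 4.12(b) (Interpretation of the results).** A response similar to that after VA1.3 is necessary for a field trial: "same or above the lower 95% CI confidence interval i.e. 49"%.

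Section 9 compares fourfold-rise percentages between the groups and gives rate ratios, both with 95% CIs, but ties no threshold to them. Section 9.5 anticipates no deviation from the statistical plan. No section says which of the three bars governs.

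**The concern.** Sections 4.11 and 7.1 both concern the response after the first dose and both use the figure 30, but they apply it to different quantities. In 4.11 it is a margin that the lower confidence bound of a difference must clear. In 7.1 it is a raw percentage in one arm. A rule on the vaccine arm alone ignores the control group of a placebo-controlled trial in an endemic city, where some placebo recipients are expected to seroconvert. A rule on a point estimate does not control the error at the boundary that the sample size was chosen to exclude.

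At stake is the trial's conclusion on immunogenicity. The same data could be reported as acceptable efficacy under 7.1 while failing the criterion the trial was sized for. A vaccine called acceptable in 7.1 that then misses the necessary condition in 4.12(b) has no defined status.

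**Working it through.** **Inputs, all from 4.11, 4.12(b) and 7.1:** one-sided alpha 0.05 (z = 1.645); power 0.90 (z = 1.282); placebo rate 5%; vaccine rate 60%; difference to exclude 30 points; 40 per arm evaluable, 44 randomised; 49% in 4.12(b); 30% in 7.1.

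**1. The plan's own figure.** With unpooled variance,

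n = (1.645 + 1.282)² × (0.60×0.40 + 0.05×0.95) / (0.55 − 0.30)² = 8.57 × 0.2875 / 0.0625 = 39.4, so 40 per group.

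This reproduces 4.11. The 30 in that section is therefore a margin on a difference.

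**2. Smallest passing result at 44 per arm.**

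- 7.1: 0.30 × 44 = 13.2, so 14/44 (31.8%).
- 4.12(b), read as an observed rate: 0.49 × 44 = 21.56, so 22/44 (50%).
- 4.11, applied as a Wald lower bound, d − 1.645 × √[pv(1−pv)/44 + pp(1−pp)/44] > 0.30. With 2/44 placebo responders, 21/44 gives 43.2 − 1.645 × 8.16 = 29.8 points (fails) and 22/44 gives 45.5 − 1.645 × 8.17 = 32.0 points (passes). The minimum runs from 19/44 with no placebo responders to 24/44 with four.

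**3. An example.** 15/44 versus 2/44 is 34.1% versus 4.5%. It passes 7.1. The difference is 29.5 points with standard error 7.81 points, so the lower bound is 29.5 − 1.645 × 7.81 = 16.7 points. It fails 4.11, and 34.1% is below 49%.

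**4. Probability of passing each bar.** Exact enumeration of two independent binomials, 44 per arm, placebo 5%:

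| True vaccine rate | 7.1 | 4.11 | 4.12(b), observed rate |
|---|---|---|---|
| 30% | 45% | 1.1% | 0.4% |
| 35% | 72% | 5.3% | 2.9% |
| 40% | 90% | 16% | 12% |
| 45% | 97% | 34% | 30% |
| 60% | >99.9% | 91% | 93% |

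The 35% row is the boundary of 4.11 (35 − 5 = 30 points). At 40 per arm that row reads 79%, 4.8% and 3.6%.

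**5. Requiring both 4.11 and 4.12(b).** At 60% versus 5% the joint probability is 89.3% at 44 per arm and 87.5% at 40. For 4.11 alone it is 91.1% and 89.1%.

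**The case against.** - **7.1 is not the field-trial rule.** A reader might infer that 7.1 would send a vaccine with a 30% response to a field trial. The text does not support that. Section 7.1 speaks only of acceptable efficacy; 4.12(b) is the gate, and it would stop 14/44 or 15/44. The 72% is the chance of an acceptable-efficacy conclusion, not of progression. This objection stands and limits the harm.
- **4.11 is a sample-size section.** It states no consequence if the bound is missed. That is true, but it says that its bound serves to establish adequate seroconversion, which is the question 7.1 answers by another rule.
- **The bars are nested.** In the enumeration no outcome passes 4.11 or 4.12(b) and fails 7.1, so a floor with a stricter gate above it would be coherent. The protocol does not describe such tiers, and a floor without a placebo term or a bound would still conflict with 4.11.
- **The 30% in 7.1 is a miscopied margin.** A reader might infer this from the shared number. The documents do not say so, and the point does not depend on it.
- **4.12(b) is ambiguous.** It speaks of a rise in titre, gives a percentage, and names neither estimator nor time point. If this trial's own lower two-sided exact 95% limit had to reach 49%, about 29/44 would be needed. The 4.12(b) figures here hold only for the observed-rate reading; the other reading widens the gap.
- **The placebo comparison is planned.** Section 9 reports it with confidence intervals, so the evidence would be visible. Only the verdict in 7.1 ignores it.

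**Conclusion.** The concern holds in this form: 7.1 sets a lenient single-arm bar that conflicts with the criterion in 4.11 and is not reconciled with 4.12(b). At 44 per arm the bars are 14/44 for 7.1, against about 22/44 for each of the other two when two placebo recipients respond. At a true 35% versus 5%, 7.1 gives a conclusion of acceptable efficacy in 72% of trials, 4.11 in about 5% and 4.12(b) in about 3%.

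The size rests on a 5% placebo rate, a Wald bound for 4.11 (which matches the stated 40 per group) and 4.12(b) read as an observed rate. If the vaccine performs as planned, at 60%, 7.1 is almost always met, and the few conflicting verdicts (11% of trials) come from trials that miss 4.11, 4.12(b) or both. The conflict matters when the true response falls short, which is when a decision rule is needed.

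**What to change.** Replace the 30%-of-vaccinees rule in 7.1 with the 4.11 criterion: immunogenicity is acceptable if the lower limit of the one-sided 95% confidence interval for vaccine minus placebo seroconversion after dose 1 exceeds 30 percentage points. State that 4.12(b) is a separate necessary condition for the field trial, and specify whether its 49% applies to the observed vaccine-arm rate and at which time point. Make the change before unblinding.

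The cost is wording only, with no added subjects, visits or assays. The bar becomes stricter than 7.1. At the planned 60% versus 5%, 4.11 alone passes 91% of trials at 44 per arm and 89% at 40. With 4.12(b) as an observed rate, both together pass 89.3% and 87.5%, slightly under the planned 90%, and the protocol should acknowledge this.

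### Sections 4.11/4.12(a) and 7.2 of the protocol set two unreconciled acceptance rules for diarrhoeal adverse events: an upper confidence bound below 20 points, and an excess below 10% of unstated type

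*Protocol*

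**What the plan says.** Three places in the protocol bear on what counts as an acceptable diarrhoea rate.

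- **Section 4.11 (Sample Size).** The endpoint is diarrhoea in the three days following either dose. The planning case is "Assuming a 10% diarrheal rate among placebo and vaccine recipients alike", and the aim is "to exclude a vaccine-placebo difference in the rate of diarrhea of greater than 20% (upper boundary of the 1-tailed 95% confidence interval") with power 0.9. From this the section concludes that "the minimum number of subjects required for each group is 39". The larger vibriocidal requirement of 40 and an allowance for dropout bring the size to 44 per group.
- **Section 4.12(a) (Interpretation of the results).** "Acceptable level of adverse events mainly diarrhea, vomiting (see 4.11) is a necessary condition for field trial". The field-trial condition therefore takes its level from 4.11.
- **Section 7.2 (Assessment of efficacy).** "a rate lower than 10% incremental rate over the placebo group will be considered acceptable level of response". This sentence does not refer to 4.11, names no confidence limit, and does not say whether the 10% is absolute or relative.

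The safety analysis in section 9 reports adverse-event percentages with 95% confidence intervals by group. It attaches no acceptance rule to them and does not mention either threshold.

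**The concern.** The same endpoint has two acceptance rules that differ in threshold (20 against 10) and possibly in kind (a confidence bound against an observed difference). The protocol does not say whether they are alternatives, whether both must hold, or which prevails.

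Occurrence of adverse events is a primary endpoint in section 4.2, and diarrhoea is the adverse event named in the synopsis safety criterion. An acceptable level is also a precondition for a field trial of a live vaccine. If the result is borderline, one section can support calling it acceptable and another calling it unacceptable. The error rates also differ: 4.11 was built to limit the chance of accepting a true 20-point excess to about 5%, and 7.2 as worded has no stated error rate.

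**Working it through.** **Inputs, all from section 4.11 unless noted.** True rate 10% in both arms; margin 20 points; one-sided 95% bound (z = 1.645); power 0.9 (z = 1.282); 44 per group planned. The 10% threshold is from 7.2. Section 4.11 names no interval method, so the bound was computed by both Wald and Newcombe.

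**Step 1. Reproduce the plan's figure.** n = (z₀.₉₅ + z₀.₉)² × [p(1−p) + p(1−p)] / margin² = 8.564 × 0.18 / 0.20² = 38.5, rounded up to 39. This matches. Power for the 20-point bound is Φ(0.20/√(0.18/n) − 1.645): 90% at 39, 91% at 40 and 93% at 44 per group.

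**Step 2. Read 7.2 as an observed absolute difference.** At 44 per arm, 4 extra vaccine cases give 4/44 = 9.1 points (pass) and 5 extra give 5/44 = 11.4 points (fail). Exact binomial enumeration at 44 per arm gives:

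| True vaccine vs placebo | 7.2 met | 4.11 met (Wald / Newcombe) | Rules disagree (Wald / Newcombe) |
|---|---|---|---|
| 10% vs 10% | 94.6% | 92.1% / 90.3% | 3% / 4% |
| 20% vs 10% | 51.4% | 39.3% / 36.3% | 12% / 15% |
| 30% vs 10% | 11.7% | 5.8% / 5.1% | 6% / 7% |

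Nearly all the disagreement runs one way, with 7.2 accepting what 4.11 rejects. At 10% vs 10% the one-sided half-width is 1.645 × √(0.18/44) = 10.5 points, so an observed excess below 10 and a bound below 20 are close to the same rule. The half-width grows as the rates rise, and the rules then separate.

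**Step 3. A discordant result.** 9/44 vs 5/44:
- Difference: 0.2045 − 0.1136 = 0.0909, so 7.2 is met.
- Wald: SE = √(0.2045 × 0.7955/44 + 0.1136 × 0.8864/44) = 0.0774; bound = 0.0909 + 1.645 × 0.0774 = 0.218.
- Newcombe: the one-sided Wilson upper limit for 9/44 is 0.3202 and the lower limit for 5/44 is 0.0564; bound = 0.0909 + √((0.3202 − 0.2045)² + (0.1136 − 0.0564)²) = 0.220.

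Both bounds exceed 0.20, so 4.11 is not met.

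**Step 4. Read 7.2 as a 10-point confidence bound.** Power = Φ(0.10/√(0.18/n) − 1.645): 44% at 40 and 47% at 44 per arm. For 90% power, n = 8.564 × 0.18 / 0.10² = 154.1, or 155 per arm. These figures apply only on this reading.

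**The case against.** The best defence is that the two rules nearly coincide and that the protocol already says which one governs. Section 7.2 uses no confidence language, and its neighbour 7.1 is likewise a plain proportion rule. Where the protocol means a bound, as in 4.11, it says so. On that reading 7.2 is an observed-difference rule that is met in about 95% of trials in the planning case and agrees with 4.11 in about 96-97% of them. Only 4.12(a) ties diarrhoea to the field-trial decision, and it cites 4.11. Section 9 also reports confidence intervals, so sampling error is not wholly out of view.

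Most of this stands, and it rules out several stronger readings that a reader might infer:

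- **That the stated power of 0.9 is wrong, or that the trial is underpowered for safety.** The 0.9 is stated for the 20-point bound and is correct for it. The 44-47% depends on a bound that 7.2 does not state.
- **That the verdict can be freely chosen after the data are seen.** The cross-reference in 4.12(a) limits this.
- **That the rules conflict equally in both directions.** A result of 5/44 vs 0/44 (+11.4 points) fails 7.2 and seems to pass 4.11, but only with a Wald bound (19.2). The Newcombe bound is 21.6, so it then fails both rules and there is no conflict.

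The defence does not remove the contradiction. Section 7.2 still declares its own acceptable level for the same endpoint without reference to 4.11, and the 9/44 vs 5/44 result splits the two rules by either interval method.

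**Conclusion.** The point holds as an unreconciled contradiction between 4.11/4.12(a) and 7.2 on a primary safety endpoint. It is not an error in the sample-size calculation.

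On the observed-difference reading the practical gap is small when the vaccine adds no diarrhoea and larger in the borderline region, where 12-15% of trials at a true 20% vs 10% would get opposite verdicts. At the 20-point excess that 4.11 is meant to exclude (30% vs 10%), 7.2 alone would accept about twice as often: 11.7% against 5-6%.

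These figures assume 44 evaluable subjects per arm, independent binomial counts, a 10% placebo rate and an absolute scale. If 7.2 were meant as a relative increase, none of them would describe it, and the text does not exclude that. The documents do not settle which threshold is clinically acceptable, and no view is taken on it here.

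**What to change.** Reconcile 4.11, 4.12(a) and 7.2 before the code is broken, so that all three carry the same rule:

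1. Name one threshold and one decision quantity: either the upper one-sided 95% bound (with the interval method named) or the observed difference. Give it on the absolute scale, for diarrhoea within three days of either dose.
2. If a second threshold is kept, say that it is an additional condition and that both must be met.
3. State the power of the rule chosen. The existing 39 per group and 0.9 serve unchanged for a 20-point bound. An observed-difference rule at 10 points should be given with its acceptance probabilities from the table above. A 10-point bound should be given with its power of about 44-47%.

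The choice of threshold is the sponsor's. The cost is a wording amendment to three sections, with no added subjects and no change to procedures or data collection. If the sponsor chooses a 10-point bound, the cost also includes a less favourable stated power.

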## 8. SAFETY

### 8.1. Adverse Events

#### Definitions

##### ADVERSE EVENTS:

An adverse event is defined as any noxious, pathologic, or unintended change in anatomic, physiologic, or metabolic functions, as indicated by physical signs, symptoms, and/or laboratory changes occurring in any phase of the clinical trial, regardless of their relationship to study medication. Adverse events include:

- an exacerbation of a pre-existing condition
- any illness happening in between the two doses' administration period
- any drug interaction
- any event related to a concomitant medication
- pregnancy

A treatment-emergent event is defined as any event not present prior to exposure to study medication or any event already present that worsens in either intensity or frequency following exposure to study medication.

##### Expected adverse events

##### Possible adverse events would include:

- 1) abdominal pain
- 2) loss of appetite
- 3) nausea
- 4) general ill feeling
- 5) fever and vomiting

Follow-up for adverse events following immunization will be conducted and recorded.

##### SERIOUS ADVERSE EVENTS:

A Serious Adverse Event means any event that results in:

- death
- is immediately life-threatening
- results in persistent or significant disability/incapacity
- requires inpatient hospitalization or prolongation of existing hospitalization
- Any other medically important condition that required intervention to prevent one of the above criteria.

Important medical events that may not result in death, be life-threatening, or require hospitalization may be considered a serious adverse event when, based upon appropriate medical judgment, they may jeopardize the subject and may require medical or surgical intervention to prevent one of the outcomes listed in this definition. Examples of such medical events include allergic bronchospasm requiring intensive treatment in an emergency room or at home, blood dyscrasias or convulsions that do not result in in-subject hospitalization, or the development of drug dependency or drug abuse.

### Assessment of Causality

The Investigator's assessment of an adverse event's relationship to study drug is part of the documentation process, but it is not a factor in determining what is or is not reported in the study. If there is any doubt as to whether a clinical observation is a treatment-emergent adverse event, the event should be reported. The relationship of administration of the study agent to the serious adverse event will be assessed as follows:

|                      |                                                                                                                                                                                                    |
|----------------------|----------------------------------------------------------------------------------------------------------------------------------------------------------------------------------------------------|
| Very Likely/Certain: | A clinical event with a plausible time relationship to vaccine administration and which cannot be explained by concurrent disease or other drugs or chemicals.                                     |
| Probable:            | A clinical event with a reasonable time relationship to vaccine administration; is unlikely to be attributed to concurrent disease or other drugs or chemicals.                                    |
| Possible:            | A clinical event with a reasonable time relationship to vaccine administration, but which could also be explained by concurrent disease or other drugs or chemicals.                               |
| Unlikely:            | A clinical event whose time relationship to vaccine administration makes a causal connection improbable, but which could be plausibly explained by underlying disease or other drugs or chemicals. |
| Unrelated:           | A clinical event with an incompatible time relationship and which could be explained by underlying disease or other drugs or chemicals.                                                            |
| Unclassifiable:      | A clinical event with insufficient information to permit assessment and identification of the cause.                                                                                               |

